#### Personalized dosing strategy

In the personalized dosing strategy arm, participants are prescribed an initial occlusion dose determined by their age, type, and severity of amblyopia, based upon dose-response functions derived from previous studies involving participants of near-identical clinical and demographic status to those enrolled in the present trial [11,12]. As participants in this arm progress through the occlusion phase, the prescribed occlusion dose is modified at each clinic visit, depending on treatment compliance, and is predicated on the notion of a total effective dose: the minimum amount of occlusion that should result in an optimal visual outcome.

The rationale underpinning treatment by a personalized dosing strategy is an attempt to define a patient’s total occlusion dose, which can then be converted to a daily patching regimen on the presumption of a fixed treatment period. We make the assumption that every patient has some optimal visual outcome that they can hope to achieve, and that there exists some total effective dose of occlusion that must be received in order to achieve it. Furthermore, we assume that any dose received by a patient in excess of this total effective dose is ‘wasted’: it does not improve the patient’s visual acuity any further, as it is impossible to improve beyond the patient’s optimal visual outcome. For example, if a patient’s total effective dose is 200 hours, then that patient will have the same visual outcome after 200, 250, or even 1,000 hours of occlusion. However, the patient’s visual improvement would be limited if fewer than this 200 hours of occlusion were achieved. Employing mathematical notation, we can say that patient *i* has some optimal visual acuity *V*_*i*_^***^, which will be achieved if, and only if, patient *i* undertakes at least *D*_*i*_^***^ hours of occlusion. Our aim is to construct a model that predicts this *D*_*i*_^***^ based on an analysis of known treatment-response functions [11,12]. To constrain the complexity of the model (and in the absence of compelling evidence to the contrary) it is assumed that the total effective dose is dose-rate independent, that is, a single occlusion dose is of equivalent effectiveness to multiple individual doses that sum to the same total number of hours.

Predictions of *D*_*i*_^***^ were derived from a normal linear interval regression model with the total effective dose of some patient *i* with initial residual amblyopia *R*_*i*_ and age *A*_*i*_ estimated by the formula:$$ {\mathrm{D}}_{\mathit{\mathsf{i}}}^{*}={\left(18.150+16.122{R}_i\hbox{--} 0135{A}_i\hbox{--} 0.547{T}_M\hbox{--} 8.028{T}_S\hbox{--} 12.176{R}_i{T}_M\hbox{--} 11.334{R}_i{T}_S+0.065{A}_i{T}_M+0.192{A}_i{T}_{\mathrm{S}}\right)}^2 $$where *T*_M_ and *T*_S_ are indicator functions taking the value 1 if the patient has mixed or strabismic amblyopia, respectively, or 0 otherwise.

In practice, participants in the personalized dosing strategy arm have their total effective dose estimated on an assumed fixed follow-up period of 12 weeks, which results in manageable dose-rates. Therefore, an individual patient’s personalized daily patching regimen will be calculated by first estimating the total effective dose and then dividing this by the number of days left in the follow-up period. For reasons of practicality, we only prescribe daily patching episodes rounded up to the nearest 30 minutes. Dose-rate can then be updated at follow-up appointments based on how much occlusion has been objectively recorded. To avoid the prescription of subtherapeutic doses of occlusion, the model is constrained such that dose-rates less than 2 hours per day are never prescribed. Of course, patients will probably be treated for a period longer than 12 weeks, as the follow-up sessions will be continued until the visual acuity criteria for study exit have been met. Therefore, once a patient passes the tenth week of follow-up, all future daily prescription calculations will assume a 2-week follow-up period until treatment is completed.

To illustrate implementation, consider a hypothetical patient who enters occlusion aged 48 months with residual amblyopia of 0.5 logMAR and amblyopia associated with anisometropia. Using the formula derived from our model, the estimated total effective dose would be 389 hours. Over a 12-week follow-up period, this requires an average daily dose of 4.6 hours per day, and so we initially prescribe 5 hours of occlusion a day. At a follow-up appointment 2 weeks later, the patient has only undertaken 30 hours of occlusion (rather than the prescribed 70). The patient’s total effective dose reduces from 389 to 359 hours, but with only 10 weeks left of the initial follow-up period the patient must now average 5.1 hours of occlusion a day. Thus, our prescribed dose-rate increases to 5.5 hours a day.

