## Discussion

The trial protocol described herein aims to compare two means of prescribing occlusion therapy for childhood amblyopia. One trial arm (standardized dosing strategy) is considered representative of current best practice in the UK, the other (personalized dosing strategy), a regimen with an empirical basis formulated using a statistical modelling approach of documented patient response data. To the best of our knowledge, the personalized dosing strategy is an entirely novel approach to undertaking occlusion therapy, with a significant potential benefit of a reduction in the amount of treatment needed. This advantage goes beyond any anticipated economic benefit and bears directly on the unpleasantness of occlusion for children and the corresponding difficulty parents have in achieving compliance (objective estimates of occlusion received are less than half those prescribed [17]). Hence, the personalized dosing strategy is underpinned by the notion of a total effective dose: a prescription of occlusion that is sufficient and not excessive and is informed on a prospective basis by an individual’s compliance (actual dose received).

It is necessary to emphasize that the implementation of a personalized dosing strategy (either that developed for the present trial or future modifications of it) is entirely dependent on the use of occlusion dose monitoring. This important advance has hitherto been entirely confined to use within formalized research studies and is not used routinely in clinical practice despite the seemingly obvious advantages it brings in providing feedback to clinicians and parents. A demonstration of the superiority of the personalized dosing strategy approach would undoubtedly provide an incentive for its take-up in the clinic.

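### At the wear the article itself reports, the personalized-arm update rule does not deliver the manageable dose-rates claimed for it, and for some eligible children it returns more than 24 hours a day

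*Protocol article*

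**What the plan says.** The section on the personalized dosing strategy in the protocol article gives the algorithm in full. A regression formula predicts the total effective dose from residual amblyopia, age and type of amblyopia. Each child has a "total effective dose estimated on an assumed fixed follow-up period of 12 weeks, which results in manageable dose-rates". The daily prescription comes from taking the total effective dose and "dividing this by the number of days left in the follow-up period", rounded up to the next half hour and never below 2 h/day. It is updated at visits from the occlusion recorded. After the tenth week, "all future daily prescription calculations will assume a 2-week follow-up period until treatment is completed". No upper bound is stated.

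The worked example follows one child for two weeks: "consider a hypothetical patient who enters occlusion aged 48 months with residual amblyopia of 0.5 logMAR and amblyopia associated with anisometropia". For this child "the estimated total effective dose would be 389 hours", and 5 h/day is prescribed. At the first visit "the patient has only undertaken 30 hours of occlusion (rather than the prescribed 70" hours, so the prescription rises to 5.5 h/day.

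The Discussion describes compliance in general: "objective estimates of occlusion received are less than half those prescribed".

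**The concern.** The rule carries any shortfall forward and spreads it over fewer and fewer days, down to 14. A child who wears about half of what is prescribed builds up a shortfall that the last fortnight of the 12 weeks must absorb. The rule guards against outputs that are too low but says nothing about outputs that are too high. Low wear is what the article expects, so this is not a rare corner of the algorithm.

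At stake is the definition of the experimental intervention. Adapting the dose to compliance is what distinguishes the personalized arm. If the rule returns hours that cannot be worn for the less compliant children, what they are actually prescribed is not defined by the text. The trial would then be comparing the standardized arm with something other than the strategy described.

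**Working it through.** **Inputs** (all from the personalized dosing section unless noted): intercept and residual-amblyopia terms "18.150+16.122{R}_i"; age coefficient printed as 0135; 84-day period; rounding up to 0.5 h; floor 2 h/day; 14-day denominator from week 10; two-weekly visits (Occlusion phase); one recorded fortnight of 30 h out of 70 h. Wear after week 2 is not in the documents and is an assumption throughout.

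**Step 1: reproduce the plan's figures.** For an anisometropic child both type indicators are 0. With residual amblyopia R = 0.5, age A = 48 months and coefficient 0.135:

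D* = (18.150 + 16.122 × 0.5 − 0.135 × 48)² = 19.731² = 389.3 h, against the stated 389.

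389/84 = 4.63, prescribed as 5. After 30 h: 359/70 = 5.13, prescribed as 5.5. Both agree with the example. Read literally, 0135 gives 41,651,392 h; 0.135 with age in years gives 659 h. Only 0.135 with age in months fits.

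**Step 2: continue the rule for the worked child.** Rate at each visit = (389 − hours recorded so far) / days left, rounded up to 0.5 h.

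| Assumed wear | Wk 0 | Wk 2 | Wk 4 | Wk 6 | Wk 8 | Wk 10 |
|---|---|---|---|---|---|---|
| 100% of each prescription | 5 | 5 | 4.5 | 4.5 | 4.5 | 4.5 |
| 30 h first, then 100% | 5 | 5.5 | 5.5 | 5 | 5 | 5 |
| 80% | 5 | 5 | 5 | 5.5 | 6 | 7 |
| 50% | 5 | 5.5 | 6 | 7 | 8.5 | 12 |
| 30/70 (42.9%) | 5 | 5.5 | 6 | 7 | 9 | 14 |
| 30 h every fortnight | 5 | 5.5 | 6 | 7.5 | 10 | 17.5 |

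At week 10 the outstanding hours are 165 in the 50% row (165/14 = 11.79), 194 in the 30/70 row (194/14 = 13.86) and 239 in the last row (239/14 = 17.07).

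**Step 3: other eligible children.** The inclusion criteria set no upper limit on severity. The R values below are illustrative.

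- Initial dose, anisometropic, 36 months: R = 0.8 gives 26.188² = 686 h, 686/84 = 8.16, so 8.5 h/day. R = 1.0 gives 29.412² = 865 h, so 10.5. R = 1.2 gives 32.636² = 1,065 h, so 13.
- Week 10 at 50% wear, anisometropic, R = 1.0: at 48 months, 772.4 h initially and 341.9 h outstanding, 341.9/14 = 24.42, so 24.5 h/day. At 36 months, 865.1 h initially and 385.6 h outstanding, 385.6/14 = 27.54, so 28 h/day.
- Initial dose, mixed or strabismic, ages 36 to 107 months, R up to 1.2: 2 to 6 h/day.
- Initial dose, anisometropic, R = 0.5, across the four ages tried (36, 48, 72 and 107 months): 2 to 5.5 h/day.

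**The case against.** Several points on the other side have force.

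**The worked child does not itself yield 17.5 h/day.** A reader might infer that it does, but the example stops at week 2. That figure needs 30 h in each of four further fortnights. Against the rising prescriptions, wear would fall from 30/70 = 43% to 30/77 = 39%, 30/84 = 36%, 30/105 = 29% and 30/140 = 21%. No section describes such a decline. The figure is one end of a range that starts near 4.5 h/day.

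**The manageability claim is about choosing 12 weeks.** For the worked child the starting 5 h/day equals the highest standardized regimen, and rising prescriptions under low wear are the intended design. So this is not a flat contradiction for that child. The defence does not cover the whole eligible group, because some severe anisometropic children start at 8.5 to 13 h/day before compliance enters.

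**The extremes are confined.** High starting doses arise in severe, mainly younger, anisometropic children, and the article gives no severity distribution, so their frequency is unknown.

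**Some children leave before week 10**, under the exit criteria on equal or stabilized acuity. This softens the point but does not remove it. The article expects treatment usually to run past 12 weeks. On its log-time figures (mean 4.0133, SD 0.801, taken as normal and in days), (ln 70 − 4.0133)/0.801 = 0.29, so about 38% would reach best acuity after day 70.

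**The formula and the example do not truly disagree.** A reader might infer so from the printed 0135. It is a lost decimal point, perhaps from typesetting or text extraction, and the restored value reproduces the example.

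**A ceiling may exist in the full protocol.** That is possible. The point is therefore put as a test of a stated claim against a stated rule, not as a missing detail. That clinicians would improvise, or that children would be harmed, is not established by the text.

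**Conclusion.** The point holds in a bounded form. At the wear the article reports, under half, its update rule does not bear out the manageability claim. The worked child reaches 12 h/day at week 10 with 50% wear and 14 h/day at the example's own ratio. With 50% wear, a 36- or 48-month-old anisometropic child with residual amblyopia of 1.0 logMAR is given more hours than a day contains. The last result needs no clinical judgement to see that the rule as written cannot be followed.

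The conclusion rests on three assumptions: wear after week 2 is a constant share of each prescription, the child is still in the occlusion phase at week 10, and the coefficient is 0.135 with age in months. With good wear, or in most mixed and strabismic children at the outset, the outputs are unremarkable beside the standardized regimens of 2 to 5 h/day. This should be corrected, because the rule defines the experimental arm and the repair is cheap. The coefficient is a minor erratum.

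**What to change.** Reconcile the manageability statement and the update rule with the worked example and with the compliance figure in the Discussion:

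1. Tabulate the rule's output at each visit over the eligible range of age, type and severity, for wear from 30% to 100% of prescription.
2. Have the clinical leads state in the protocol what applies where the output cannot be worn. No dose or limit is proposed here.
3. Record the computed and the prescribed dose at every visit, so that departures from the rule can be counted and described.
4. As a minor correction, print the age coefficient as 0.135 and state that age is in months, so that the formula gives 389 h for the worked child.

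The cost is a protocol amendment, one small table and one extra recorded field. No design change or additional participants are needed.

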### Recruitment sites

Potential study participants are initially identified from new patients attending orthoptic departments at Hillingdon Hospital, Hillingdon, UK and Princess Alexandra Hospital, Harlow, UK.

### Trial phases

#### Initial assessment phase

Attending patients undergo a full orthoptic and ophthalmic examination, including cycloplegic refraction. Where clinically significant refractive error is found, spectacles are prescribed (full corrections for astigmatic, anisometropic myopic and mild or moderate hypermetropic (+2.00 to +5.00) and within 2 dioptres of the full correction for high hypermetropic errors). Clinically significant refractive error is defined as:≥1.50 dioptres sphere bilateral hypermetropia,≥1.50 dioptres sphere bilateral myopia,≥0.75 dioptres cylinder bilateral astigmatism,All astigmatism in combination with hypermetropia,≥1.00 dioptres sphere anisometropia.

The parents or guardians of those children meeting the study’s eligibility criteria are provided with an information sheet and, subject to verbal consent, invited to attend an appointment (start of trial) with a research orthoptist ([name] or [name]). They are asked to bring with them (but not to have their child previously wear) any spectacles dispensed as an outcome of the current consultation.

#### Optical treatment phase

Written informed consent is sought from the parents or guardians of all potentially participating children at the outset of this phase. Except for those children not prescribed spectacles in the initial assessment phase (who progress directly to the occlusion phase), participants are instructed to wear their spectacles full time and to return for vision assessment at 6-weekly intervals from week 0 (onset of spectacle wear) until 18 weeks of optical treatment is complete (a period that allows for all significant improvement attributable to spectacle wear to have occurred [15]). If there is a significant improvement (≥0.1 logMAR) between weeks 12 and 18, the participants are asked to wear their spectacles for further 6-week periods until significant gains have ceased. If participants have worn spectacles for refractive correction prior to study entry, the number of weeks for which spectacles were previously worn is documented; a minimum of 18 weeks (in total) wear is required before progression to the next study phase. It is anticipated that around 20 to 25% of participants will, by the end of this phase, have obtained equal eye acuity and will leave the trial at this point.

As a safeguard, should significant deterioration in acuity occur (defined as loss of more than 0.20 logMAR from any previous testing), the child will undergo a repeat cycloplegic refraction and the prescription will be changed if there is a significant difference from the initial prescription, before recommencing in this study phase. If no discrepancy is observed, in the presence of sustained deterioration in vision, the child shall be withdrawn from the trial. If a pathological cause of the vision loss is suspected, the child is referred back to the ophthalmologist at the local site for continued clinical care.

#### Occlusion phase

On entering this phase, study participants are randomly assigned (stratified by geographic site and amblyopia type) to either the personalized or standardized dosing strategy arms of the trial using an online true random number generator [16].

Participants will have their visual acuity recorded every 2 weeks until the trial endpoint is reached. To provide a check against the unmasked nature of the study design, visual acuity is further recorded at the end of the occlusion phase by an examiner masked to the participants’ treatment arms.

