#### Analyses

The primary study objective of comparing time to best visual acuity between the two treatment groups, along with the secondary objective of comparing compliance, will be analyzed via standard *t* tests (to compare length of time and compliance) and Levene’s test (to compare variance in time). Suitable nonparametric alternatives will be used should concerns arise regarding the necessary distributional assumptions for these methods. The secondary objective to determine the relationship between changes in visual acuity and dose, amblyopia type, and age, will be investigated using standard regression modelling approaches.

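### Allocation is stratified by site and amblyopia type, but the primary t test adjusts for neither stratum nor for recorded severity and age: valid, with a precision loss of unknown and possibly small size

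*Protocol article*

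**What the plan says.** Under Occlusion phase, children are "randomly assigned (stratified by geographic site and amblyopia type") "using an online true random number generator". There are two sites (Recruitment sites) and three amblyopia types (the dose formula separates anisometropic, mixed and strabismic). Blocking, or any other device to force balance within strata, is not mentioned.

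Under Analyses, the primary comparison of time to best visual acuity, together with compliance, "will be analyzed via standard *t* tests (to compare length of time and compliance) and Levene’s test (to compare variance in time"). The only fallback is this: "Suitable nonparametric alternatives will be used should concerns arise regarding the necessary distributional assumptions for these methods". Regression appears once, for the secondary objective on acuity change, which "will be investigated using standard regression modelling approaches".

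Under Personalized dosing strategy, the starting dose in that arm is "determined by their age, type, and severity of amblyopia, based upon dose-response functions derived from previous studies". The standardized arm also sets its daily dose by acuity at the end of the optical phase. The authors therefore have type, age and severity for every child before treatment starts, and regard them as relevant to response.

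**The concern.** Stratifying the allocation and then leaving the strata out of the analysis is a mismatch. If balance within strata is forced, the difference between arms no longer carries between-stratum variation, but the t test's standard error still includes it. The interval is then too wide and the test conservative. Age and severity are not stratified, so chance differences between arms in these factors stay in the estimate as noise that a model could remove.

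Precision is what is at stake. The trial has 120 children and the covariates already exist, so any gain from conditioning on them needs no extra child or measurement. The article names the test and its fallback, so this is a stated choice and not a detail left to a later document.

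**Working it through.** **1. The plan's own figure.** Endpoint determination and sample size calculation gives 60 per arm, 95% power, type I error 0.05, d = 0.605, and log time with mean 4.0133 and SD 0.801. Sidedness is not stated.

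- Noncentrality: d × √(n/2) = 0.605 × √30 = 3.314, on 118 degrees of freedom.
- One-sided 0.05 (critical t 1.658): power 95.1%. The stated figure reproduces.
- Two-sided 0.05 (critical t 1.980): power 90.8%. It does not reproduce; 72 per arm would be needed for 95%.
- Days: exp(4.0133) − exp(4.0133 − 0.605 × 0.801) = 55.3 − 34.1 = 21.2, matching the stated 21.

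The calculation contains no stratum or covariate term.

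**2. Effect of adjustment.** If the covariates explain a share R² of the variance of log time, the residual SD falls by √(1 − R²) and the effective d becomes 0.605/√(1 − R²). Five degrees of freedom are spent: site 1, type 2, acuity 1, age 1. R² is an assumption throughout.

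| Assumed R² | Effective d | Two-sided power | One-sided power |
|---|---|---|---|
| 0 (unadjusted) | 0.605 | 90.8% | 95.1% |
| 0.02 | 0.611 | 91.3% | 95.4% |
| 0.04 | 0.617 | 91.8% | 95.7% |
| 0.05 | 0.621 | 92.1% | 95.9% |
| 0.10 | 0.638 | 93.4% | 96.6% |
| 0.20 | 0.676 | 95.7% | 97.9% |
| 0.30 | 0.723 | 97.5% | 98.9% |

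**3. Which R² is plausible?** The document's evidence concerns dose. Its formula (age coefficient read as 0.135, which reproduces the worked example of 389 hours) gives, at 0.5 logMAR and 48 months, 389 h for anisometropic, 263 h for mixed and 233 h for strabismic amblyopia. Time is another matter, because daily dose follows severity in both arms. Take an anisometropic child of 48 months, assume full compliance, and let residual amblyopia stand in for acuity in the standardized bands:

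- 0.2 logMAR: 222 h. Personalized: 222/84 = 2.64, rounded up to 3.0 h/day, so 222/3.0 = 74 days. Standardized at 2 h/day: 222/2 = 111 days.
- 0.8 logMAR: 604 h. Personalized: 604/84 = 7.19, rounded up to 7.5 h/day, so 604/7.5 = 81 days. Standardized at 5 h/day: 604/5 = 121 days.

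The dose rises 2.7-fold (604/222), but predicted time rises by only about 9% in each arm. Over assumed spreads of severity, age and type, again at full compliance, slopes common to both arms explain about 2 to 5% of 0.801². Incomplete compliance could move this either way.

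**4. Conservatism.** This was simulated with 120 children, six equally likely strata, strata and other covariates each explaining 10% of variance (assumed), two-sided 0.05 and 5,000 runs.

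| Allocation within strata | Type I error, t test / adjusted | Power, t test / adjusted |
|---|---|---|
| Blocks of 4 (assumed) | 3.5% / 4.7% | 92.2% / 95.7% |
| No blocking | 4.7% / 4.7% | 90.6% / 94.5% |

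The t test is conservative only under forced balance. It loses power in both cases.

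**The case against.** The strongest reply is that the t test is valid and the gain may be trivial. Most of this stands. Type I error is not inflated under either allocation scheme. Chance imbalance in age or severity is random error that the t test's standard error already covers, so it is not bias.

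A reader might take the variance of predicted log dose, divide it by 0.801², and infer that covariates explain a large share of log time, worth many extra children per arm. The documents do not support this. The ratio compares hours with days, and the dosing rules in both arms largely cancel the link between severity and time. Nor can one infer that the planned test is conservative, since forced balance within strata is nowhere stated. Quoting only the two-sided 90.8% would also borrow urgency from the unstated sidedness, which is a separate matter. On the one-sided reading that reproduces the plan's figure, the gain is smaller throughout.

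It may also be said that a condensed article leaves model terms to an analysis plan. That would hold had the article been silent, but it names an unadjusted test and a nonparametric fallback.

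Finally, the primary objective includes reduced variance in time. The personalized arm may reduce variance precisely by evening out time across severity, type and age. Applying Levene's test to model residuals would remove part of that effect, so the fix must leave that test alone.

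**Conclusion.** The point holds as a loss of efficiency. The allocation uses site and type, the primary comparison uses neither, and severity and age go unused as well. It is not a validity error.

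The size is unknown, because the document gives no R² for log time. At R² of 0.02–0.04, which the dosing rules make plausible under full compliance, the gain is 0.5 to 1.0 points of two-sided power and about 0.3 to 0.7 points one-sided. At R² of 0.10 to 0.30 it would be 2.6 to 6.7 points two-sided and 1.5 to 3.8 points one-sided. These figures assume d = 0.605, 60 analysed per arm, log time as the outcome and covariate slopes common to both arms. The case for the change is that it is cheap and settles the adjustment in advance in an unmasked trial, not that a large gain has been shown.

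**What to change.** Make the primary comparison of mean time a linear model of log(time) on arm, site, amblyopia type, start-of-occlusion acuity (continuous) and age (continuous), and keep the unadjusted t test as a sensitivity analysis. Log time is the scale the sample size section already uses. Keep Levene's test for the variance objective on unadjusted log times, not on model residuals.

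The cost is a change of analysis wording, about five degrees of freedom out of 118, and slightly more analysis work. No new data are needed: site and type are required for stratification, acuity at the end of the optical phase for the standardized regimen, and age for the personalized formula.
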